### **16.2 Secondary and tertiary outcomes:**

Toxicity would be assessed at clinical visits . Relation between biomarkers and disease control ( clinical benefit rate and progression free survival) would be explored by using a suitable statistical test selected on the basis of type of data ( continuous, ordinal) and its distribution. Multiplicity bonferroni correction would be used.

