### 7.3 Tertiary objective (both stages)

To study gene expression changes in the tumor tissue during MCT-E to identify responders and mechanisms of resistance.

1. To analyze HPV, markers of inflammation, cell proliferation, apoptosis and hypoxia to evaluate the association with treatment response.
2. To identify the transcriptomic alterations and to delineate the genes/gene clusters which are differentially regulated in response to the treatment.
3. To carry out global miRNA profiling in tissue and serum samples to identify miRNAs differentially regulated in response to the treatment.

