### Microarray based Gene Expression Analysis

Global gene expression profiling will be carried out on the tissue samples. RNA will be isolated from the tumor tissue samples using the QIAGEN RNeasy Mini kit according to the instructions of the manufacturer. RNA with RIN value more than 7 will be used for analysis. Gene expression arrays from Agilent Technologies (4x44k) will be used for proposed analysis. The comparison will be carried out analyze the differentially expressed genes before starting the therapy and at the end of the therapy. Results of microarray data will be validated by TaqMan quantitative real-time PCR and immunohistochemistry .

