### Microarray based global miRNA profiling of serum.

Total RNA will be extracted from 400µl of serum from patients using a mirVana PARIS kit (Ambion) and finally eluted into 100 µl of preheated (95°C) elution solution according to the manufacturer's protocol. The miRNA microarrays manufactured by Agilent Technologies will be used. There are a total of 1205 human and 144 human viral miRNAs on the Agilent Human miRNA Microarray. Total of 100 ng RNA will be labelled and hybridised using the Human microRNA Microarray Kit protocol. Differentially expressed miRNAs will be validated by TaqMan quantitative real-time PCR (TaqMan MicroRNA Assays; Applied Biosystems).

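### Section 16.2 names Bonferroni for secondary and tertiary outcomes without defining the family; if it covers the 44,000-probe arrays, it suits gene discovery poorly for moderate effects and responder comparisons

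*Protocol*

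**What the plan says.** Section 16.2 of the protocol is headed "Secondary and tertiary outcomes". It says that toxicity is assessed at visits and that "Relation between biomarkers and disease control ( clinical benefit rate and progression free survival) would be explored" with a test chosen by data type and distribution. It ends: "Multiplicity bonferroni correction would be used". It gives no family of tests, number of tests or alpha.

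The tertiary objective in section 7.3 is "To study gene expression changes in the tumor tissue during MCT-E to identify responders and mechanisms of resistance". Its sub-aims include to "delineate the genes/gene clusters which are differentially regulated in response to the treatment" and to profile miRNA in tissue and serum.

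Section 12.2 gives the platforms: "Gene expression arrays from Agilent Technologies (4x44k) will be used for proposed analysis" and "There are a total of 1205 human and 144 human viral miRNAs on the Agilent Human miRNA Microarray". On follow-up of array hits it says: "Results of microarray data will be validated by TaqMan quantitative real-time PCR and immunohistochemistry". The miRNA part also plans PCR validation. The gene comparisons it spells out are within patient: before against the end of therapy, day 7 against baseline, and progression against day 7. Neither array part names a multiplicity method.

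**The concern.** Bonferroni limits the chance of even one false positive across the whole family. That suits a short list of confirmatory tests. A genome-wide screen followed by validation has different costs: a false lead can be dropped at PCR or immunohistochemistry, but a gene missed on the array is never followed up.

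If the rule in 16.2 governs the arrays, it sets a very strict per-gene threshold on the work that justifies three biopsies per patient, which the protocol defends by what they would show about mechanism and resistance. The cost would be a shorter gene list than the same samples could support, with the heaviest loss where responders are compared with non-responders.

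**Working it through.** **Inputs from the protocol**
- About 44,000 probes per gene array, and 1205 + 144 = 1,349 miRNA features (section 12.2).
- At most 30 + 76 = 106 patients (section 15).
- Usable samples will be fewer. Section 12.2 excludes tissue with less than 60% tumour from the arrays and requires a RIN above 7, and each paired contrast needs both biopsies. No pass rate is given.

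**Assumptions (not in the protocol)**
- Family-wise alpha 0.05, two-sided, with one contrast as the family. Several contrasts in one family would make Bonferroni stricter.
- Standardised effect d of 0.5 to 1.0.
- 1% to 5% of probes truly changed.
- Usable n as shown, and an equal responder split.

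The protocol states no power for this objective, so there is no figure to reproduce.

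**Thresholds**
- Gene array: 0.05/44,000 = 1.14e-6.
- miRNA array: 0.05/1,349 = 3.7e-5.

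**Power.** This is the probability that a noncentral t variable exceeds the two-sided critical value.
- Paired: df = n - 1, noncentrality d x sqrt(n).
- Two equal groups: df = n - 2, noncentrality d x sqrt(n/4).

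**False discovery rate (FDR) threshold.** Solve p0 x t / (p0 x t + p1 x power(t)) = 0.05 for the per-test threshold t, where p1 is the share of changed probes and p0 = 1 - p1.

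**Worked case: 60 pairs, d = 0.5.** The noncentrality is 0.5 x sqrt(60) = 3.87. At 1.14e-6 the critical t on 59 df is 5.43, and power is 8.5%. For FDR with p1 = 1%, t = 2.7e-4 and power is 50%. With p1 = 5%, t = 2.0e-3 and power is 74%.

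**Gene array, power per truly changed probe** (FDR ranges run from 1% to 5% of probes changed)

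| Comparison | n | d | Bonferroni | 5% FDR |
|---|---|---|---|---|
| Paired | 46 | 0.5 | 3% | 24-50% |
| Paired | 60 | 0.5 | 8.5% | 50-74% |
| Paired | 80 | 0.5 | 23.5% | 78-91% |
| Paired | 30 | 0.8 | 9% | 62-84% |
| Paired | 46 | 0.8 | 45% | 94-98% |
| Paired | 60 | 0.8 | 76% | 99% or more |
| Paired | 76 | 0.8 | 94% | over 99% |
| Responder v non-responder | 76 | 0.5 | 0.2% | 0.2-3% |
| Responder v non-responder | 76 | 0.8 | 5% | 34-59% |
| Responder v non-responder | 76 | 1.0 | 20% | 73-88% |

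**Expected yield, 60 pairs, d = 0.5.** Changed probes number 440 (1% of 44,000) to 2,200 (5%). Bonferroni finds 440 x 0.085 = 37 to 2,200 x 0.085 = 187. FDR finds about 440 x 0.50 = 220 to 2,200 x 0.74 = 1,628.

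**miRNA array, 60 pairs.** Bonferroni gives 30% at d = 0.5 and 95% at d = 0.8. The number of tests does not enter the FDR equation, so the FDR values are again 50-74% and 99% or more. The loss is smaller than for genes.

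**The case against.** The strongest reply is that section 16.2 never mentions arrays. The Bonferroni sentence directly follows the analysis of biomarkers against disease control, which matches the limited marker panels of the secondary objectives, where Bonferroni is reasonable. The array contrasts are described in section 12.2 and are different analyses. The error rate for a microarray is often left to a statistical analysis plan, and one may exist that is not shown here. Bonferroni is also valid: it biases nothing and inflates no false-positive rate.

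Much of this stands. Coverage of the arrays is inferred from the word tertiary in the heading. A reader might infer that Bonferroni is fixed for every secondary and tertiary outcome, arrays expressly included; the text does not say so. Silence on array multiplicity would not be a fault by itself. However, the protocol does name a method under a heading that includes the array objective, so its scope should be stated.

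A reader might also infer that almost no power remains for gene discovery. That is too strong, because the comparisons spelled out in section 12.2 are paired and larger paired changes survive. Nor would pathway work be left without input: even the 60-pair, d = 0.5 case is expected to yield some 37 to 187 true probes.

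**Conclusion.** The point holds in limited form. The scope of Bonferroni in section 16.2 is undefined and, by its heading, extends to the arrays. Applied there, it is a poor choice for a screen with planned validation. The loss is large for moderate paired effects, when few usable pairs remain, and for responder comparisons at differences of about 0.8 to 1.0. It is small for large paired effects and milder for the miRNA array. FDR control is no rescue everywhere: at a responder difference of 0.5 with 76 patients, power is 3% or less under either rule.

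The sizes rest on the assumed effects, usable n, responder split and share of changed probes. The direction does not depend on their exact values. The objective is tertiary and no primary result is affected, so this is a cheap improvement.

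**What to change.** In section 16.2, limit Bonferroni to the short serum and tissue marker panels and say which tests form that family. State that the gene-expression and miRNA arrays use the Benjamini-Hochberg procedure at a 5% false discovery rate within each contrast, with selected hits going to the PCR and immunohistochemistry validation already planned.

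This costs one sentence and needs no extra patients, samples or assays. The downside is that about 5% of listed genes are expected to be false leads. The planned validation filters those taken forward; genes listed but not validated should be reported as unconfirmed.

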## **17 Data Collection Methods**

Patient eligibility for the trial will be documented in a separate eligibility checklist (Appendix ). Each trial participant will be assigned a study specific identification which will be used for referring to that patient in the study duration subsequently. A study specific CRF (Appendix ) will be used for these patients to capture the baseline clinical and laboratory parameters. Patients will be assessed on day D8 of the 1st cycle of chemotherapy using a custom designed proforma (Appendix ) which will capture the toxicity encountered in the patient in the last 7 days. After the first cycle another proforma (Appendix ) will be used to capture toxicity in the last chemotherapy cycle. Other procedures and tests done for this protocol including imaging will be detailed in the existing departmental forms. A copy of these forms will be kept along with the patient record for the trial. Results of hematological and biochemical tests will be recorded in the toxicity recording proformas mentioned above.

## **18 Data Management**

The trial specific CRF and other forms will be kept in a secure almirah in the Department of Medical Oncology. Data entry will be done on a trial specific electronic database maintained on the hospital local area network. Double data entry will be done by two trial coordinators. Data management will be done in accordance with the hospital data safety and monitoring board guidelines.

## **19 Quality assurance**

### ***Chemotherapy Quality Assurance***

The standards proposed by ASCO/ONS Chemotherapy Safety Standards for Drug preparation and administration will be followed. At least two medical personnels will verify the patient identification, drug names, dose, route of administration and expiration dates/times and appearance and physical integrity of the drug to be administered prior to each cycle. They will also sign the chemotherapy delivery chart independently to verify the above.

### ***Toxicity Assessment***

All toxicities will be graded as per the CTCAE v 4.03 criteria. Disagreement between grading by two observers in the toxicity levels will be resolved through discussion with a reason behind disagreement noted for each event and the resolution adopted. In order to ensure complete documentation of toxicity a prespecified toxicity CRF will be used and recorded for each patient.

## **20 Monitoring**

### **20.1 Data Monitoring**

The institutional data monitoring and safety board (DSMB) will be responsible for oversight of the data. A trial specific data monitoring committee may be formed at the discretion of the DSMB to monitor the trial progress.

### **20.2 Interim Analysis**

As this is a stage I/II study , interim analysis will be done at after completion of stage 1.

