## **4.2 Metronomic chemotherapy (celecoxib and oral methotrexate) in Head and Neck cancers**

Metronomic chemotherapy has been developed as a cost effective palliative chemotherapy option in head and neck cancers. Recently we conducted a randomized study of metronomic combination of celecoxib ( 200 mg BD) and oral weekly methotrexate ( 15 mg/m^2 weekly). In this study metronomic chemotherapy was compared against cisplatin chemotherapy. Both the median progression free survival and overall survival were significantly better than cisplatin.. Patients in the metronomic arm had significantly longer PFS (median 101 days, 95% CI: 58.2–143.7 days) compared to the cisplatin arm (median 66 days, 95% CI; 55.8–76.1 days) ( $p = 0.014$ ). The overall survival (OS) was also increased significantly in the metronomic arm (median 249 days, 95% CI: 222.5–275.5 days) compared to the cisplatin arm (median 152 days, 95% CI: 104.2–199.8 days) ( $p = 0.02$ ). This is probably the only trial except EXTREME study ( cetuximab study) which showed a survival benefit of a chemotherapy over cisplatin. As discussed in above section previous studies of combination chemotherapies had failed to show a survival benefit over cisplatin. Additionally these results of metronomic chemotherapy were achieved with much lower side effects and lesser amount of hospital visits. This is an oral chemotherapy regimen and the cost is around 1000-2000 INR per month as opposed to cost of combination chemotherapy ( Paclitaxel+ carboplatin) been around 15,000-20,000 INR month and cost of cetuximab been nearly 4.0 lakh INR / month. Metronomic chemotherapy hence seems an affordable, accessible, safe and efficacious regimen in oral cancers. However the cohort of patients used in our metronomic randomized study had to be either chemonaive or need to have a failure free period of 3 months or more.

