### 4.4 Rationale for combination of erlotinib and celecoxib with methotrexate (MTX)

Combination of erlotinib and celecoxib has a strong biological rationale. Metronomic chemotherapy is presumed to act by antiangiogenesis. Hence combination of metronomic with erlotinib would overcome one of the mechanism of resistance of erlotinib. Abcc2, Abcc3, and Abcg2 are multidrug transporters which together mediate the rapid elimination of MTX and 7OH-MTX from the cell. Abcg2 transporter is expressed in head and neck cancer s in around

50-65% of patients. its considered an unfavourable prognostic factor. Erlotinib reverses ABCB1- and ABCG2-mediated MDR in cancer cells through direct inhibition of the drug efflux function of ABCB1 and ABCG2. Hence combination of erlotinib and metronomic chemotherapy is a logical step and may lead to improvement in outcomes.

The use of this regimen on compassionate basis in poor risk head and neck cancers has been described by VP ( author) in his previous institute.( data accepted for publication). In a small prospective study in pretreated patients this combination had a response rate of 46.7% and had a promising median PFS of 148 days (95%CI 95.47-200.52 days). The study met its primary endpoint of improving median PFS over 120 days. Upfront combination of MCT with erlotinib (MCT-E) studied by the author resulted in a 6 month survival of 80%.(accepted for publication). These results need confirmation in a large study, with translational research to identify the mechanism of action, resistance and biomarkers for efficacy prediction.

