#### **4.7 Need for novel design for finding optimal biological and effective metronomic dose of oral methotrexate**

Metronomic administration is actually a schedule. Same drugs when administered in maximum tolerable dose (MTD) would have different action and the same drugs when administered in 1/10th to 1/3rd of doses of MTD would have different mechanism of action. This phenomenon is seen in multiple chemotherapeutic drugs like paclitaxel, cyclophosphamide, vinca alkaloids and in methotrexate.

The doses selected for metronomic studies have been arbitrary. Doses of 10-33% of MTD have been selected. The dose of methotrexate in Head and neck cancer metronomic was also selected in a similar way. This approach has been criticised by Lam et al. He stressed in his review on having a rationale design for finding an optimal dose of metronomic schedule.

Traditional optimal dose finding designs are based on tolerance to chemotherapy. Doses which lead to acceptable dose limiting toxicities are selected hence these chemotherapy regimes are labelled as maximum tolerable dose (MTD) chemotherapy. The issue in metronomic schedules is that toxicity is not a concern. In our own experience with methotrexate and celecoxib only 18.9% patients had grade 3-4 adverse events (all inclusive) as opposed to 31.4% in cisplatin arm. Not only that toxicity is not a concern but the metronomic effect of a drug is supposed to happen at much lower doses than the MTD hence toxicity as used in traditional dose finding design cannot be used as a parameter for optimal dosing of a metronomic schedule. (Figure 1)

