## 15 Sample size calculation

**Total sample size** : Stage 1 ( 20-30 patients) + Stage 2 ( 76 patients). In stage the continuous reassessment model will be used hence the sample size would be maximum of 30 and minimum around 20. The exact calculations done in both stages are described below in details.

Stage 1 : Flexible-finite sample based approach will be adopted to select the circulating endothelial cells (CEC) interval boundaries and further to use optimum interval design. During the trial, we will continuously update the posterior estimates of decline in CEC and clinical benefit rate and assign patients to the most appropriate dose combination (Figure 1). The Bayesian adaptive screening design will be used to simultaneously select among possible treatment dose combinations. The design is based on formulating the selection procedure as a Bayesian hypothesis testing problem in which the superiority of each treatment combination is equated to a single hypothesis. During the trial conduct, we intend to use the current values of the posterior probabilities of all hypotheses to adaptively allocate patients to treatment combinations. The dose-finding decision will be decided on the twin endpoints the clinical benefit rate at 2 months and proportional decline in CEC at D8 of first cycle. Figure 2 will be used for decision making.

Stage 2: It was assumed that the 3-month progression-free survival (PFS) rate of a standard cancer therapy is 0.50 (H0). An improvement to 0.60 would be considered clinically significant (H1). Assume both the null and alternative PFS distributions follow an exponential distribution. The 1-sided type I error rate of 0.05 and type II error rate of 0.1. Prior assumption includes a fixed enrollment rate of 3 patients per month. We require a stop of 3 months at the end of Stage 1. The library("OptInterim") has been used to calculate the sample size. A 20%extra patient would be taken to account for lost to follow up data. Hence **a total of 76 ( 63 patients +13 patient) sample size is found suitable to carry out the study for stage II with single arm drug therapy.**

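### The only interim look follows Stage 1 and has no criteria, and Stage 2 (76 patients) has none, so no observed toxicity rate of the three-drug regimen obliges a pause

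*Protocol*

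**What the plan says.** - **Interim look.** Section 20.2 is one sentence: "interim analysis will be done at after completion of stage 1". It does not say what is examined, against what limit, or what follows.
- **Stage 1 decision.** Section 15: "The dose-finding decision will be decided on the twin endpoints the clinical benefit rate at 2 months and proportional decline in CEC". Section 16.1 names the same two endpoints for the OBD. Section 4.7 explains why toxicity is not used: "toxicity as used in traditional dose finding design cannot be used as a parameter for optimal dosing of a metronomic schedule".
- **Stage 2.** Section 15 sets 76 patients and states "Prior assumption includes a fixed enrollment rate of 3 patients per month". No look within Stage 2 is described. Between the stages, "We require a stop of 3 months at the end of Stage 1"; Section 14 labels that block as time for selecting the dose.
- **Tolerability evidence.** Section 4.7: "In our own experience with methotrexate and celecoxib only 18.9% patients had grade 3-4 adverse events", against 31.4% on cisplatin in the same trial. Section 4.2 says those patients "had to be either chemonaive or need to have a failure free period of 3 months or more". For the three-drug regimen, Section 4.4 reports that "this combination had a response rate of 46.7% and had a promising median PFS of 148 days", with no toxicity rate. Section 4.3 calls erlotinib 150 mg with celecoxib up to 400 mg/day, given with re-irradiation, well tolerated. Section 27 says the same of the regimen from Indian data, but expects more mucositis, loose motions and rash.
- **Safeguards.** Toxicity must settle before each cycle (Section 11.1). Rash and diarrhoea have treatment triggers (Section 11.2). Patients come off treatment or are dose-reduced for toxicity (Sections 11.3, 11.4). The institutional DSMB has oversight (Section 20.1). SAEs go to the IRB, and a DSMB hazard judgement is one SAE criterion (Section 21). Audits and IRB reports are six-monthly (Sections 22, 23.1).

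**The concern.** Erlotinib 150 mg daily is given at every methotrexate level. Excess toxicity from adding it would belong to the whole regimen, and lowering methotrexate may not remove it. The rate that supports low concern comes from a doublet without erlotinib, in patients with a longer failure-free period than the early failures enrolled here (Section 10.1). Followed to the letter, the plan can declare an OBD and then accrue 76 patients without anyone being required to compare the regimen's Grade 3 or higher rate with a limit. A pause is possible, but only at discretion. Between two six-monthly reports about 3 × 6 = 18 patients enter. Much outpatient Grade 3 rash, diarrhoea or mucositis would not meet the Section 21 definition of an SAE.

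**Working it through.** **1. The plan's own figures.** 63 × 1.20 = 75.6, so 76 patients. 76 / 3 = 25.3 months of accrual (the concept sheet says 24). Only the enrolment number and rate are needed here.

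**2. Is there a trial-level limit?** Sections 11.1 to 11.4 act on single patients. Section 14 and the 3-month stop in Section 15 serve dose selection. Sections 20.1, 21, 22 and 23.1 provide oversight and reporting. None states a rate or count. Under the text as written, the probability of an obligatory pause is 0 at every toxicity rate.

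**3. What would pass without a required comparison?** Expected patients with Grade 3-4 events among 76: 76 × 0.189 = 14; 76 × 0.314 = 24; 76 × 0.40 = 30; 76 × 0.50 = 38. The first two rates are in Section 4.7. The last two are assumptions.

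**4. What would a simple rule do?** The event is Grade 3 or higher toxicity in the first two cycles (8 weeks). The protocol gives no acceptable rate, so the reference is assumed and varied. Prior Beta(2·ref, 2·(1−ref)); the boundary at n is the smallest x with P(rate > ref | x, n) > 0.90. For ref = 0.314 the prior is Beta(0.628, 1.372). At n = 10 the posterior probability is 0.861 for x = 5 and 0.954 for x = 6, so the boundary is 6/10.

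Lag: 8 weeks / 4.345 weeks per month × 3 per month = 5.5, say 6 patients entered but not yet evaluable. With 70 evaluable, 76 have entered, so the last useful look is at 60.

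| Reference | Stage 1 boundaries (6, 12, 18, 24, 30) | Stage 2 boundaries (10, 20, …, 60) |
|---|---|---|
| 31.4% | 4, 7, 9, 11, 13 | 6, 10, 13, 17, 21, 24 |
| 25% | 4, 6, 8, 10, 11 | 5, 8, 11, 14, 17, 20 |

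Probability of crossing, from an exact sequential binomial calculation:

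| True rate | Stage 2, ref 31.4% | Stage 1 to 30 patients, ref 31.4% | Stage 2, ref 25% |
|---|---|---|---|
| 18.9% | 0.007 | 0.018 | 0.054 |
| 25% | 0.047 | 0.068 | 0.232 |
| 31.4% | 0.210 | 0.201 | 0.584 |
| 40% | 0.662 | 0.520 | 0.930 |
| 50% | 0.970 | 0.862 | 0.998 |

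If Stage 1 ends near 20 patients (looks at 6, 12, 18), the Stage 1 figures at reference 31.4% are 0.345 at 40% and 0.656 at 50%. With a 40% reference, Stage 2 gives 0.038, 0.222 and 0.708 at true rates of 31.4%, 40% and 50%.

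When a Stage 2 review is triggered at reference 31.4%, on average 28.9 patients are evaluable at a true 40% and 21.9 at 50%. Adding 6, about 35 and 28 have entered, out of 76.

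**5. Unneeded pauses over both stages**, 1 − (1 − P₁)(1 − P₂), with Stage 1 run to 30:
- Reference 31.4%: 1 − 0.982 × 0.993 = 0.025 at a true 18.9%; likewise 0.11 at 25% and 0.37 at 31.4%.
- Reference 25%: Stage 1 probabilities are 0.040 and 0.155, giving 0.09 at a true 18.9% and 0.35 at 25%.

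**The case against.** **Boundaries may sit elsewhere.** Numerical limits are often kept in a SAP or DSMB charter, and neither is at hand. This stands as a limit on the point: if a charter holds them, one cross-reference settles it. But Section 20.2 itself fixes when the trial looks, and it fixes that as once, before the larger stage. A trial-level safety look cannot be supplied afterwards by analysts.

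**Toxicity was left out on purpose.** A reader might infer that omitting it from Stage 1 dose choice is the error. The documents do not support that. Methotrexate only goes down from 15 mg/m², a dose already used (Section 4.2), and Sections 4.7 and 4.8's preceding design discussion give the reasoning. That argument covers methotrexate, though, and not the erlotinib added at a fixed dose.

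**Oversight exists.** A reader might infer that safety is unmonitored. It is not: the DSMB can act at any time, and Section 21 adds event-level SAE reporting and a hazard judgement. What is missing is an action limit.

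**The regimen is described as well tolerated.** Sections 4.3 and 27 say so, and Section 27 also expects no rise in haematological, neurological or renal effects. This tempers the concern. It does not replace a Grade 3-4 rate for the triplet, and Section 27 leaves open which regimen the earlier data describe.

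**The size rests on assumptions.** This is correct. The 31.4% is a cisplatin-arm rate with no time window, from a different population, and 40-50% are chosen values. They show how a rule behaves and predict nothing about this regimen.

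**Conclusion.** The point holds in a limited form. The protocol fixes one look without criteria after Stage 1 and none across 76 Stage 2 patients, so no observed toxicity rate of erlotinib, celecoxib and methotrexate obliges a pause. It is a worthwhile, cheap improvement and does not invalidate the design. Nothing in the documents shows that the triplet is too toxic, and 31.4% should not be read as an acceptable limit.

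The gain depends on the true rate and the chosen reference. With 31.4% and a 0.90 cut-off, a Stage 2 review is very unlikely at the doublet's 18.9% (0.007) and likely at 40% (0.66) or 50% (0.97). These figures assume independent patients, a constant rate, 3 entries per month and an 8-week window. A trigger means a pause for review, not the end of the trial.

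**What to change.** In Sections 20.1 and 20.2, have the existing DSMB review the number of patients with Grade 3 or higher toxicity (CTCAE 4.03) in the first two cycles, counting everyone who took a dose:
- every 6 evaluable patients in Stage 1, dose levels pooled;
- every 10 in Stage 2, up to 60.

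Accrual pauses for review when a prespecified beta-binomial boundary is crossed. Any crossed Stage 1 boundary is reviewed before Stage 2 opens; the 3-month stop exceeds the 8-week window, so the last Stage 1 counts will be complete. The dose-finding model needs no toxicity term.

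Before the first look, the DSMB fixes the event definition and a matching reference rate. Treatment-related events are preferable, because disease-related events could inflate an all-cause count: Section 4.2 gives a median survival of 110 days for early failures on the doublet. The 31.4% is all-inclusive and would not suit that definition unchanged. The definition should name rash, which is absent from the monitored list in Section 21.

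**Cost.** A few sentences and one boundary table, or one sentence pointing to a charter. No new visits are needed: toxicity is already charted at C1D8 and on day 1 of each cycle. It adds up to 5 counts in Stage 1 and 6 in Stage 2. The price is the unneeded pauses worked out above: about 2.5%, 11% and 37% at true rates of 18.9%, 25% and 31.4% with the 31.4% reference, or about 9% and 35% at 18.9% and 25% with a 25% reference.
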